The exclusion criteria for the recruitment of SUs include: (I) having a legal requirement to attend as part of a Drug Rehabilitation Requirement or Alcohol Treatment Requirement as this may impact engagement results, (II) being unable to provide informed consent due to a lack of mental capacity, (III) little/no understanding of spoken English as all sessions will be carried out in English and instructions for subjective measures used in this project are in English, (IV) being left- and mixed-handed: an outcome measure utilized (i.e., the EEG frontal alpha asymmetry) is modulated by handedness direction (i.e., left-handed, right-handed) providing empirical justification for the practice of excluding left-handers and mixed-handers when exploring relationships between this neural marker and other variables [34], (V) not being registered with a general practitioner (GP)/unable to provide GP details: we will require GP details to notify them in case of any incidental EEG findings. Furthermore, participants who disclose in the consent form that they had experienced a Stroke, Traumatic Brain Injury, or Epilepsy will be contacted by the research team to discuss if they can wear an EEG cap and participate in the measurements. Our inclusion and exclusion crit﻿eria are broadly based on the eligibility criteria for SUs to attend most groups in the service. We expect participants to either be abstinent or present with low to moderate substance use. Participants would also likely be housed and have access to public funds. While this presents a sample with diverse substance use patterns and individual circumstances, this is more representative of the cohort that would use this type of intervention. The diversity in participants may aid determining feasibility and acceptability of the intervention and provide value in planning further more focused studies. Regarding SG, only members of WDP staff will be included in this group.

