### Analysis strategy regarding the secondary study aims

The strategy for the secondary aims entails data collection and analysis of quantitative and qualitative data from the EEG, questionnaires, a behavioral task, and a semi-structured interview. To analyze the effects of an MT program (GMT/IMT) in addition to ST compared to ST only on secondary dependent variables, descriptive, graphical, and inferential analyses will be used. Effect sizes will also be computed where relevant. The present research is a feasibility study and because of the small sample size, certain inferential statistics requirements cannot be satisfied. Therefore, results related to the secondary aims are to be considered—and will be presented as—preliminary. Descriptive analyses will be conducted by calculating means and standard deviations at each time point. Inferential statistical analyses will be conducted to evaluate the effect of MT (GMT/IMT) in addition to ST on mental health and brain processing by comparing the data between pre- and post- intervention in each group using a parametric or non-parametric test (e.g., paired t-test or Wilcoxon Signed-Rank test, respectively) depending upon the data distribution. The dependent variables that we will measure are pre-post intervention changes in the following outcomes: (I) score of the PHQ-9 and resting-state FAA for depressive symptoms; (II) score of the BSCS and resting-state beta frequency band for the craving state experienced over a 24-h period; (III) score of the GAD-7 and resting-state FMT for anxiety symptoms; (IV) score of the TOP for substance use, days of primary substance used, average usage of primary substance per day, physical wellbeing health, psychological health, and overall quality of life; and (V) P3 EEG event-related potential amplitude and behavioral accuracy during a Go/No-Go task for the inhibitory control. The statistical procedure to analyze data from pre-post intervention questionnaires involves both within-subject (or repeated-measures design) and between-groups (or independent design). Indeed, a pre-post intervention comparison of scores from the questionnaires will be performed for each group (GMT, IMT and ST) with a paired-samples t-test. In case the assumptions of normality and homogeneity of the data will be violated, a non-parametric Wilcoxon Signed-Rank test will be performed. The difference scores obtained from this repeated-measures design, will be used for the independent design analysis: pre-post intervention difference scores in the questionnaires administered to the MT groups (GMT and IMT) will be compared with pre-post intervention difference scores in the questionnaire administered to the ST group utilizing independent t-test. In case the assumptions of normality and homogeneity of the data will be violated, a non-parametric Mann–Whitney test will be performed.

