
For the resting-state EEG data (alpha—FAA -, beta, and theta—FMT—bands) pre-post intervention comparisons will be performed utilizing z-scores from a Normative EEG database (NG software) [54]. Furthermore, to represent the pre-post intervention difference in the topographic distribution of EEG power in the selected frequency bands a paired-samples t-test will be performed for each of the three groups. If deviations from normality will be found in the data, a non-parametric Wilcoxon Signed-Rank test will be performed. Between-group power differences will be calculated as well, by comparing differences in the topographic distribution of the EEG power in participants who received MT (GMT and IMT) alongside ST vs participants who received ST only through an independent t-test. If deviations from normality will be found in the data, a non-parametric Mann–Whitney test will be performed. Relationships between changes in the pre-post intervention questionnaire scores (PHQ-9, GAD 7, BSCS, VAS, HAQ-II) and changes in the respective EEG measures (see above) will be tested using Pearson's correlation coefficients with 95% confidence interval [16]. Likewise, we will implement the same correlation procedure to test the relationship between pre-post intervention changes in inhibitory control (P3 ERP amplitude and accuracy on “no-go” trials) and changes in the scores of the Brief Substance Craving Scale. Changes in the pre-post MT (GMT and IMT) sessions scores from the craving thermometer will be analyzed graphically (i.e., scatterplot). Those who attend more than two sessions but disengage before the study ends will have the measures up to the point of their disengagement included in data analysis.

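### The change-on-change correlations rest on Pearson's r alone, with no rank-based alternative, so in a sample of at most 15 one extreme participant can produce an interval that excludes zero (minor)

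*Protocol article*

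**What the plan says.** The section on the analysis strategy for the secondary aims plans four t-tests, and each has a rank test in reserve.

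- Questionnaires, within group: "In case the assumptions of normality and homogeneity of the data will be violated, a non-parametric Wilcoxon Signed-Rank test will be performed".
- Questionnaires, MT against ST: "In case the assumptions of normality and homogeneity of the data will be violated, a non-parametric Mann–Whitney test will be performed".
- Resting EEG, within group: "If deviations from normality will be found in the data, a non-parametric Wilcoxon Signed-Rank test will be performed".
- Resting EEG, MT against ST: "If deviations from normality will be found in the data, a non-parametric Mann–Whitney test will be performed".

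Relationships between questionnaire changes (PHQ-9, GAD-7, BSCS, VAS, HAQ-II) and the matching EEG changes "will be tested using Pearson's correlation coefficients with 95% confidence interval". P3 amplitude and no-go accuracy against the BSCS follow suit: "Likewise, we will implement the same correlation procedure to test the relationship between pre-post intervention changes in inhibitory control". Neither sentence carries a distribution check or an alternative. The general sentence in that section about choosing a parametric or non-parametric test concerns pre-post comparisons, not correlations.

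The Participants section expects people who are abstinent or have low to moderate use, and comments: "While this presents a sample with diverse substance use patterns and individual circumstances".

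**The concern.** Parts (b) and (d) of the study's expectations, at the end of the study aims, are stated as correlations. Falls in anxiety, depression and craving should go with neural change, and better inhibitory control should go with its neural marker and possibly with craving. The coefficient chosen is therefore the one that speaks to mechanism.

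Pearson's r is built from products of deviations, so a person far from the rest on both axes can dominate it when there are few points. The planned interval then describes that person more than the sample. An association of this kind, reported with an interval excluding zero, could be carried into the larger trial that the article's conclusion has in view. The article guards its mean comparisons against awkward distributions but not its correlations, and gives no reason for the difference.

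**Working it through.** **Inputs from the protocol article.** Total n = 15, five per arm. The craving VAS is collected in GMT and IMT only, so n is at most 10. The HAQ-II is collected in IMT only, so n is at most 5. The article does not say whether correlations pool the arms; n = 15 assumes that they do. The 95% interval implies a two-sided 5% level. No SDs of change and no error calculation for the correlations are given, so there is no figure of the plan's own to reproduce.

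**1. Critical value.** With df = 13, t = 2.160, so |r| must exceed 2.160 / √(2.160² + 13) = 0.514.

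**2. One extreme participant, by hand.** Take 14 people with unit SD on both measures and exactly zero correlation. Their sums of squares are 13 each and their cross-product is 0. A person at (d, d) adds (14/15)d² to all three sums.

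- d = 4: (14/15) × 16 = 14.93, so r = 14.93 / (13 + 14.93) = 0.53, which is above 0.514. The Fisher interval is tanh(0.597 ± 1.96/√12), or 0.03 to 0.82. It excludes zero.
- d = 3: (14/15) × 9 = 8.4, so r = 8.4 / 21.4 = 0.39, which is below 0.514.

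At n = 10 the same (4, 4) person gives 14.4 / (8 + 14.4) = 0.64, against a critical value of 0.632.

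**3. The same by simulation** (40,000 samples, n = 15, the other 14 people unrelated):

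| Position of the one person | Pearson significant | Spearman significant |
|---|---|---|
| 3 SD on both | 29% | 8% |
| 4 SD on both | 61% | 8% |
| 5 SD on both | 87% | 8% |

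**4. Type I error with no planted person** (n = 15, true correlation 0, nominal 5%). Shared spread means x = s·z₁ and y = s·z₂, with one s per person and z₁, z₂ independent standard normal. These patterns are assumptions.

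| Assumption | Pearson | Spearman |
|---|---|---|
| Independent normal | 5% | 5% |
| Independent exponential, t with 3 df, or lognormal | 5.0 to 5.7% | about 5% |
| Independent Cauchy (extreme case) | 7.4% | 5.2% |
| One third 3 times as variable, one measure only | 5% | 5% |
| One third 1.5 times as variable, both measures | 6.5% | 5.5% |
| One third 2 times as variable, both | 9.5% | 6.4% |
| Half with 0.3 times the spread, both | 14% | 8% |
| One third 3 times as variable, both | 16% | 8% |
| Bivariate t with 3 df | 18% | 7% |

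**5. What ranks do not cure.** The article carries baseline forward when the week-8 battery is missed, which puts that person at zero change on both axes. With 5 of 15 at (0, 0), Pearson rejects in 11.6% of samples and Spearman in 10.9%. If pooled arms differ by 1 SD on both measures, both reject in about 10%. In the case of one third at 3 times the spread, a permutation p-value for Spearman still gave 7.8%; a bootstrap interval gave about 6%.

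**The case against.** A reader might infer that the missing fallback makes these tests run at about three times their nominal error. The document does not support that. Its t-test fallbacks are triggered mainly by non-normality, and non-normality with independent variables leaves Pearson at 5 to 7%. The 14 to 18% figures need the same people to be much more variable on both the symptom change and the EEG change. The article says that the sample is diverse. It gives no SDs, and nothing in it says that abstinent people change less in FAA, FMT or beta power. This objection stands, so the error can be given only as a conditional range.

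The 4 SD participant is placed by construction, and no probability is attached to such a person. This also stands: the example shows fragility, not an error rate.

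The article admits that some inferential requirements cannot be met, and it labels secondary results preliminary. The main aim is feasibility, and the in-session hyperscanning is a separate route to mechanism. That lowers the severity. It does not alter how the interval is computed.

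Diagnostics for correlations are often left to a fuller document. That would excuse silence, but here the article names the method and gives its neighbours a fallback that the correlations lack.

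**Conclusion.** The point holds as a minor one. Two parts need no assumption about the sample: the correlations are Pearson only while all four t-tests have a rank alternative, and at n = 15 a single person about 4 SD out on both measures is enough to push the interval off zero.

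The size of any general inflation is not settled by the document. It runs from none (about 5%) through about 10% to about 14 to 18%, depending on how far the same people are more variable on both measures, and assuming that the arms are pooled. Spearman stays at about 7 to 8% in the stronger cases, so it reduces the problem without removing it. The n = 15 figures do not apply to the VAS or the HAQ-II.

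**What to change.** In the secondary-aims analysis section, amend the two correlation sentences as follows.

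- For all change-on-change correlations, report Spearman's rho with a bootstrap interval beside Pearson's r. At the least, name it as the fallback, as is done for the t-tests.
- Show a scatterplot for each correlation, with the range of each coefficient when participants are left out one at a time.
- State that no conclusion about mechanism will be drawn from an association that depends on one participant.
- For the HAQ-II, with at most 5 people, describe the data only.

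The cost is a few lines of text and minutes of analysis. Spearman's rho is slightly less efficient if the changes are truly bivariate normal. Carried-forward zeros stay a problem under either coefficient, so mark those participants on the scatterplots.

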**Methods:**

Fifteen participants, from a community service based in London, will take part in a mixed-methods non-blind randomized-controlled trial. Ten participants will receive six-weekly sessions of music therapy in addition to the standard treatment offered by the CSMTS—five of them will receive individual music therapy and five of them will receive group music therapy—while a further five participants will act as a control group receiving standard treatment only.

Satisfaction and acceptability will be evaluated in focus groups with service users and staff members following the final treatment session. Moreover, attendance and completion rates will be monitored throughout the intervention. Subjective and behavioral indexes will be assessed before and after the interventions to explore the effects of music therapy on craving, substance use, symptoms of depression and anxiety, inhibitory control, and will be correlated with associated neurophysiological signatures. In-session analysis of two individual music therapy sessions will serve to explore how music and emotion are processed in the brain within the therapy. The data collected at each step will be included in an intention-to-treat analysis basis.

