We expect that an MT intervention, carried out alongside the ST, will (a) be feasible and acceptable for individuals receiving community-based substance misuse treatment; (b) lead to a decrease in the symptoms of anxiety, depression and craving that correlates with changes in the underlying neural processes; (c) improve treatment outcomes for SU in CSMTSs; (d) improve inhibitory control that correlates with a change in the underlying neural process and, potentially, with changes in the craving intensity.

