### Sample size and dosage

Secondary purposes will be investigated within the frames of a feasibility study that include, as a corollary, the recruitment of a relatively small sample size to have preliminary data to determine whether interventions and research procedures are appropriate, acceptable, and practical [61].

Therefore, conclusions regarding mental health clinical endpoints as well as the therapeutic relationship and the role of music technology will be interpreted with care and presented as preliminary. Presently, positive results regarding the effectiveness of MT, as compared to a ST provided by the community, reflecting an improvement in the mental health of SUD participants have not been reported yet; for this reason, notwithstanding the small sample size limitation, it is essential to fill this gap in the literature. Additionally, analysis of the primary and secondary study aims will be performed on an intention-to-treat basis to manage drop-outs and missing data. A total of 6 IMT and GMT sessions will be offered. Patients with fewer sessions will not be excluded from data analysis (intention-to-treat principle; [62]). Nevertheless, to minimize missing data imputation, for participants not attending the post-treatment test battery at week 8, the last observation carried forward (i.e., in this case, baseline measurements at week 1) will be used.

Whilst depressive [26, 27], anxiety [26, 28, 29] and craving [30–32] symptoms have been shown to improve after MT in individuals with SUD, this will be a first attempt to study these dimensions in a community setting by measuring their neural correlates.

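### Baseline carry-forward puts week-8 non-attenders at (0,0) in the symptom–EEG change correlations and can create an association with no true link; how arm is handled is not stated.

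*Protocol article*

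**What the plan says.** **Correlations.** In the protocol article, under the analysis strategy for the secondary aims, changes in questionnaire scores are related to changes in the matching EEG measure by Pearson's "correlation coefficients with 95% confidence interval". For P3 amplitude and no-go accuracy against the Brief Substance Craving Scale (BSCS), "we will implement the same correlation procedure to test the relationship between pre-post intervention changes in inhibitory control". No group, stratum or adjustment is named. Nearby tests do name theirs, for example "a paired-samples t-test will be performed for each of the three groups".

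**Missing week-8 data.** Under Sample size and dosage, the article declares an intention-to-treat basis for primary and secondary aims and adds that "the last observation carried forward (i.e., in this case, baseline measurements at week 1) will be used". The correlations are not exempted.

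**Purpose.** Study aims and specific objectives expects music therapy to "lead to a decrease in the symptoms of anxiety, depression and craving that correlates with changes in the underlying neural processes". The Background presents pre-post self-report combined with EEG as one of two angles on mechanisms of change.

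**Size.** Of the MT participants, "five of them will receive individual music therapy and five of them will receive group music therapy"; "a further five participants will act as a control group receiving standard treatment only".

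**The concern.** The week-8 battery contains the questionnaires, the resting EEG and the Go/No-Go recording. A participant who misses it and whose data are kept therefore has a change of exactly zero on both members of each pair. A cluster at the origin, set against attenders who have moved on both axes, looks like a relationship.

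The Discussion section on neural correlates predicts that both members move: PHQ-9 down with frontal alpha asymmetry (FAA) up, GAD-7 down with frontal midline theta (FMT) up, BSCS down with beta power down, and P3 and no-go accuracy up with BSCS down. The spurious sign would in each case be the sign expected if symptom change tracked neural change. The artefact would thus favour the hypothesis the correlation is meant to examine.

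A second, conditional source is arm. If MT and standard treatment (ST) participants are placed in one correlation and MT shifts both measures, the separation between arms adds a correlation of its own.

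**Working it through.** The article gives no effect size, SD, dropout rate or expected correlation for this analysis, so there is no figure to reproduce. The inputs from the document are 10 MT and 5 ST participants, Pearson's r, a 95% interval (two-sided 5%), and change = 0 on both measures for a carried-forward participant. Assumed: normal changes, a true within-arm correlation of 0, the size of the change, and the number of non-attenders.

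**Step 1: carried-forward zeros, one group.** Let a share q sit at (0,0) and let attenders have mean change m (in SD) on both measures. The covariance is q(1−q)m² and each variance is (1−q) + q(1−q)m², so

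r = q·m² / (1 + q·m²).

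For 3 of 10 MT participants, q = 0.3:
- m = 1: 0.3/1.3 = 0.23
- m = 1.5: 0.675/1.675 = 0.40

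**Step 2: arm shift, pooled, no dropout.** With p = 10/15, p(1−p) = 2/9, and shift d (in SD) on both measures,

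r = (2/9)d² / (1 + (2/9)d²).

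- d = 1: 0.222/1.222 = 0.18
- d = 1.5: 0.5/1.5 = 0.33

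Simulated false-positive rates for the pooled test are about 5.5% at 0.5 SD, 7.4% at 0.8 SD, 10% at 1 SD and 25% at 1.5 SD. If only one of the two measures moves (1.5 SD), the rate is 5.0%.

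**Step 3: both together.** 100,000 simulated trials per setting, 3 MT participants carried forward, MT change of 1 or 1.5 SD on both measures, ST change of 0:

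| Reading of the plan | Mean r, 1 SD | False positives, 1 SD | Mean r, 1.5 SD | False positives, 1.5 SD |
|---|---|---|---|---|
| All 15 pooled | 0.25 | 17% | 0.43 | 39% |
| MT only (n = 10) | 0.27 | 13% | 0.45 | 27% |
| All 15, arm-adjusted | 0.18 | 10% | 0.33 | 20% |
| Observed pairs, arm-adjusted (n = 12) | 0.00 | 5% | 0.00 | 5% |

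Effects are coded in the same direction; opposite directions only change the sign of r.

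**Step 4: sensitivity.**
- At 0.5 SD with the same three zeros, the first three readings give about 7% to 9%.
- With no mean change at all, the zeros leave mean r at 0 but raise pooled rejection to 8.1% (3 of 15) or 11.3% (5 of 15).
- With a common 1 SD change in every arm, no treatment effect and 3 of 15 zeros, the arm-adjusted analysis still gives mean r 0.20 and 10.3% rejection.

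Arm adjustment alone therefore does not remove the effect of the zeros.

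**Step 5: what the sample can show.** The |r| needed for p < 0.05 is 0.51 at n = 15, 0.63 at n = 10 and 0.88 at n = 5. By arm (n = 5), an observed r of 0.5 has the interval tanh(0.549 ± 1.96/√2) = −0.68 to 0.96.

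**The case against.** **Arm handling is unstated, not wrong.** A reader might infer that the plan pools all 15 participants and ignores arm. The text does not support that: it is silent. An MT-only analysis fits hypotheses worded as effects of MT, and a per-arm analysis is also possible; neither contains an MT-versus-ST shift. The craving VAS is collected only in the MT arms and HAQ-II only in the individual-therapy arm, so the arm component cannot reach them. This objection stands and makes the arm component conditional. It does not help with the zeros, which remain under each of these readings.

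**Not every non-attender becomes (0,0).** Under Recruitment, a withdrawing participant may have their data destroyed, and early individual-therapy dropouts may be replaced, up to twice. This also stands: the point concerns non-attenders whose data are kept. The carry-forward rule is written for exactly those people.

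**The assumed effects are large.** A simultaneous 1 to 1.5 SD change in symptoms and EEG is a lot, and placing all three non-attenders in MT is an assumption. At 0.5 SD the inflation is small.

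**Results are labelled preliminary.** The article says so twice, and the 95% interval would show the imprecision. That label warns of small numbers. It does not disclose a bias whose direction follows from a stated rule.

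**The remedy departs from the intention-to-treat statement.** True, so it must be written as an exception. A correlation between two observed changes is not a randomised comparison, and an imputed pair carries no information about it.

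**Conclusion.** The concern holds for the carry-forward rule as fixed. For participants who miss week 8 and whose data are kept, the rule supplies identical zero changes on both axes. When attenders change on both measures, the planned correlation is biased in the predicted direction, with about 10% to 39% false positives under the stated assumptions (three such MT participants, 1 to 1.5 SD change, no true within-arm link).

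The arm component is secondary and depends on pooling, which the article does not state. It applies only to PHQ-9/FAA, GAD-7/FMT, BSCS/beta and P3 or no-go accuracy/BSCS.

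The feasibility aim is unaffected. This is worth correcting because the article gives these correlations a role in explaining mechanism.

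**What to change.** In the analysis strategy for the secondary aims, state that the change-score correlations use only participants with both week-1 and week-8 values observed on both measures. Under Sample size and dosage, record this as an exception to carry-forward.

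For the four pairs that include ST participants, report one arm-adjusted (pooled within-arm) correlation with its 95% interval, and mark points by arm on the plot. State the number of pairs used.

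**Cost.** Wording in two places, one degree of freedom for MT versus ST or two for three arms, and the loss of any participant without week-8 data. With three dropouts and one degree of freedom for arm, |r| must reach about 0.60 for p < 0.05, against about 0.53 with all 15. The estimate then describes attenders only, remains exploratory, and cannot establish mechanism at this size.

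### Two rules for early leavers conflict: an attendance threshold of more than two sessions in the secondary analysis, and intention-to-treat with no exclusion for few sessions elsewhere

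*Protocol article*

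**What the plan says.** **The threshold.** The protocol article's section *Analysis strategy regarding the secondary study aims* ends with a rule for leavers. It keeps whatever was measured before departure, and it names the people to whom this applies: "Those who attend more than two sessions but disengage before the study ends". It makes no provision for leavers with two or fewer sessions.

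**The opposite rule.** The section *Sample size and dosage* states that "analysis of the primary and secondary study aims will be performed on an intention-to-treat basis to manage drop-outs and missing data". It adds "Patients with fewer sessions will not be excluded from data analysis". For anyone who misses the week 8 battery, "the last observation carried forward (i.e., in this case, baseline measurements at week 1) will be used". No session threshold and no restriction by arm is attached. The abstract's methods paragraph agrees: "The data collected at each step will be included in an intention-to-treat analysis basis".

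**Related provisions.** Attendance sheets are completed after group (GMT) and individual (IMT) music therapy sessions only. Standard treatment varies from week to week, with about three key work sessions expected over six weeks. The *Recruitment* section replaces IMT participants who drop out in the first two weeks, at most twice. It does not say whether the replaced person stays in the analysis. The same section lets a withdrawing participant have their data destroyed.

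**The concern.** Both rules cover the secondary aims, and they cannot both be followed. An analyst could leave early leavers out under one section and keep them with a zero change under the other, and could make that choice after seeing the data.

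The threshold also depends on behaviour after randomisation. If *sessions* means music therapy sessions, it can act only in the two MT arms, and control participants who disengage stay in. The MT group that is compared with standard treatment is then selected for attendance and the control group is not. If people who leave after one or two sessions do worse than those who stay, the comparison of pre-post differences tilts towards MT. These preliminary results are meant to inform a larger trial, so a tilt of this kind would be carried forward.

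**Working it through.** The protocol gives no figure for this point, so there is none to reproduce. The check is a comparison of the two rules, followed by an illustration.

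**Step 1: the rules side by side.** Table 1 schedules the pre-post battery at baseline and week 8 only, with no visit between.

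| MT participant who disengages | Threshold rule | *Sample size and dosage* rule |
|---|---|---|
| Two or fewer sessions, no week 8 data | Left out (implied) | Included, change = 0 |
| Two or fewer sessions, week 8 data obtained | Left out (implied) | Included, observed change |
| More than two sessions, no week 8 data | Included, but no change score exists | Included, change = 0 |

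The rules give different results in every row.

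**Step 2: inputs for the illustration.**
- MT arms: 10 people, five IMT and five GMT (abstract: "Ten participants will receive six-weekly sessions of music therapy in addition to the standard treatment offered by the CSMTS").
- Control arm: 5 (abstract: "a further five participants will act as a control group receiving standard treatment only").
- *k* = number of MT participants who leave after two or fewer sessions and miss week 8. The protocol gives no drop-out rate; *k* = 1 to 4 is assumed.
- *d* = mean change among the other 10 − *k* MT participants, all assumed to have week 8 data.

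**Step 3: MT mean change under each rule.**
- No exclusion, baseline carried forward: *d* × (10 − *k*)/10.
- Threshold: *d*, from 10 − *k* people.
- Ratio of threshold to no exclusion: 10/(10 − *k*).

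| *k* | MT n, threshold | MT n, no exclusion | Mean, threshold | Mean, no exclusion | Ratio |
|---|---|---|---|---|---|
| 1 | 9 | 10 | *d* | 0.9*d* | 1.11 |
| 2 | 8 | 10 | *d* | 0.8*d* | 1.25 |
| 3 | 7 | 10 | *d* | 0.7*d* | 1.43 |
| 4 | 6 | 10 | *d* | 0.6*d* | 1.67 |

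The session threshold leaves the control group at 5 throughout.

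**Step 4: how likely the rules are to diverge.** With early drop-out probability *p* (assumed) and independent participants, the chance of at least one early leaver among 10 is 1 − (1 − *p*)^10. This is 65% at *p* = 10%, 89% at 20%, 97% at 30% and 99% at 40%.

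**Step 5: direction.** Let the early leavers' true mean change be *e*. The true MT mean is ((10 − *k*)*d* + *ke*)/10, and the threshold estimate is *d*. The error is *d* − ((10 − *k*)*d* + *ke*)/10 = *k*(*d* − *e*)/10. It favours MT only if leavers improve less than those who stay, and it is zero if they improve equally. The ratios in Step 3 therefore measure how far the two rules differ, not a known bias.

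**The case against.** **The exclusion is implied, not stated.** The sentence contains neither *only* nor an exclusion, and the explicit statement elsewhere is that nobody is excluded for few sessions. That is right, and the point should be put as an implied exclusion that another section contradicts. The contradiction remains, because the threshold does nothing if everyone is included anyway.

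**The sentence may concern session-level data.** It directly follows the sentence on the craving thermometer, which is used only in the MT arms. Read that way, it would not touch the comparison with standard treatment. This reading is possible, but the sentence speaks of measures and data analysis in general and closes the whole secondary-aims section. *Sessions* is also undefined, and standard treatment has key work sessions. Music therapy sessions is still the natural reading, since only these have a fixed, logged count.

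**Retention.** A reader might infer that feasibility results are inflated, for example that retention would read 3/3 = 100% instead of 3/5 = 60% if two of five leave early. The documents do not support this. The threshold sits under the secondary aims. The main-aim section takes retention from attendance sheets and the case management system, and no section removes early leavers from its denominator. The exit questionnaire also records why people disengage.

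**Size on the PHQ-9.** A reader might also infer a specific spurious gain. If completers in every arm improve by 4 points and MT has no effect, deleting MT leavers while carrying baseline forward for a control fraction *f* gives a gap of 4*f*: 0.8 points at 20% and 1.6 at 40%. These are upper-end figures. They apply one rule to MT and the other to control, although the carry-forward rule is not limited to one arm. They assume that no MT participant leaves after session two, and the 4 points are assumed. If leavers in fact improved as much as completers, the whole gap would come from the carry-forward in the control arm and none from the threshold.

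**Secondary and preliminary.** The protocol presents these results as preliminary because the sample is small. That lowers the severity, but a caution about small numbers does not cover selective inclusion.

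**Conclusion.** The inconsistency is real and of moderate severity. Two stated rules give different analysis sets, and different change scores for the same leaver (none against zero). The discrepancy is 1.11 to 1.67 times in the MT mean change for 1 to 4 early leavers among 10. This assumes that those leavers miss week 8 and that all other MT participants have week 8 data. At an assumed early drop-out of 10% to 40%, at least one such leaver is likely (65% to 99%).

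Bias in favour of MT is a conditional conclusion: it needs *sessions* to mean music therapy sessions and early leavers to do worse than those who stay. The affected outcomes are secondary and labelled preliminary, so this falls short of a defect that undermines the study's main aim.

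**What to change.** 1. Delete the more-than-two-sessions condition from the secondary-aims analysis section.
2. State one analysis set for the secondary aims, consistent with *Sample size and dosage*: all randomised participants in their allocated arm, whatever the number of sessions attended, except data withdrawn at the participant's request as the *Recruitment* section allows.
3. State one missing-data rule for week 8 and apply it to all arms.
4. State that IMT participants who are replaced after early drop-out stay in that set. Deleting the threshold alone leaves this open.
5. If a summary of those with more than two sessions is wanted, label it supplementary.

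The cost is a few sentences of wording, with no new data or visits. The choice should be fixed before outcome data are seen.
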